### Statistical analysis

All data will be analyzed with respect to the normality of distribution using the Shapiro-Wilk test. Statistically significant differences between the experimental groups will be determined using analysis of variance, followed by a suitable post hoc test, if necessary. The significance level will be set at α = 0.05. By assuming normality in the distribution of the data, two-way ANOVA offers a high power for the design of this trial.

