Concerning muscle spasm [11-17], a reduction was found in one study that used red laser (300 mW, 10 J/cm^2^) intraorally [16], two studies that used infrared laser (100 mW, 120 12 J, 4 J/cm^2^ and 300 mW, 54 J) both intraorally and extraorally [13,17], and one study that used infrared laser (100 mW, 12 J, 4 J/cm^2^) either extraorally or intraorally [14].

The aim of the proposed project is to carry out a randomized, controlled, double-blind, clinical trial evaluating the effects of LLLT on pain, swelling and muscle spasm following surgical removal of impacted third molars. Comparisons will be made of two sites (intraoral versus extraoral) and different laser wavelengths (red versus infrared).

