### Study design and composition of study sample

The study design will consist of five treatments evaluated on two occasions (at 2 and 7 days following surgery). Table 1 shows the scheme for repeated-measures analysis of variance. Because the measures of pain, swelling and mouth opening have low variability when using the proposed scales, 40 degrees of freedom will be sufficient to control for residual variance. Thus, a minimum sample size of 50 subjects (10 in each group) is sufficient. Thus 50 patients undergoing treatment at the center for the removal of impacted lower third molars will participate in the study.

**Table 1 T1:** Scheme for repeated-measures analysis of variance

**Causes of variation**	**Degrees of freedom**
Treatment	4
Period	1
Treatment × period	4
Residual	40
Total	49

In addition, as this work predicts a two-factor (two wavelength), two-group (two irradiation sites) analysis, there will be 20 patients in each group (10 in each experimental subgroup) and 20 in control group. The power analysis (Figure 1) shows that for medium and large effect size, the test power will remain above 0.8 for 20 subjects in each group.

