### Randomization and composition of groups

After undergoing a clinical evaluation by the dental surgeons, patients who meet the eligibility criteria will be divided into five experimental groups (Figure 2) based on a randomization method involving raffle numbers. Randomization will be conducted by a researcher not involved in the recruitment and treatment of the participants. Concealed allocation will be performed using a set of random numbers placed in sealed opaque envelopes. The laser operator will open the envelope containing the procedure to be performed on each patient immediately following third molar surgery. Sealed envelopes awaiting new subjects will be kept in a safe place and given to the operator as the sessions are scheduled. The 40 patients will be allocated into four experimental groups or a control group as follows: Group 1 (660 nm laser, applied intraorally, n = 10), Group 2 (808 nm laser, applied intraorally, n = 10), Group 3 (660 nm laser, applied extraorally, n = 10), Group 4 (808 nm laser, applied extraorally, n = 10), Group 5 (control; no irradiation, n = 20).

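### The protocol does not fix one analysis model: Table 1 includes the control as a fifth treatment, but the wavelength-by-site analysis described after it has no cell for the 20 controls

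*Protocol article*

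**What the plan says.** Protocol article, Study design and composition of study sample: "Table 1 shows the scheme for repeated-measures analysis of variance". The table lists treatment (4 df), period (1), treatment by period (4) and residual (40), total 49. Four df for treatment means five levels, so the control is one of them.

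The paragraph after the table says that "this work predicts a two-factor (two wavelength), two-group (two irradiation sites) analysis". It counts 20 patients per group, made up of subgroups of 10, plus 20 controls, and claims power above 0.8 for medium and large effects with 20 per group.

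Randomization and composition of groups lists four laser arms of 10 (for example "Group 1 (660 nm laser, applied intraorally, n = 10") and an unirradiated control of 20.

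Background gives the aim as evaluating the effect of LLLT on the three outcomes and continues: "Comparisons will be made of two sites (intraoral versus extraoral) and different laser wavelengths (red versus infrared". The Discussion adds a comparison of four LLLT parameter sets.

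Statistical analysis tests group differences "using analysis of variance, followed by a suitable post hoc test, if necessary", states "The significance level will be set at α = 0.05", and closes with "two-way ANOVA offers a high power for the design of this trial". It does not say which two factors are meant.

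**The concern.** The design is a 2 x 2 factorial (wavelength by site) plus one control arm outside the factorial. The article describes two models for it and does not choose between them. They use different patients and test different hypotheses:

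- **Treatment by period:** all five arms enter. The treatment test is a 4-df omnibus test, which does not say whether laser, wavelength or site is responsible.
- **Wavelength by site:** only the four laser arms can enter, so laser against no laser is not estimable.

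If this stays open, the model can be settled after the data are seen, and one of the two candidates cannot address the first aim. The sample-size reasoning also relies on groups of 20. Laser groups of that size exist only when arms are pooled over site or wavelength, yet no pooled comparison is named as a test.

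**Working it through.** **1. The plan's own figure.** The stated power above 0.8 cannot be reproduced from the text: the effect sizes have no numbers, the test is not identified and Figure 1 is not shown. As an illustration, taking f = 0.25 and 0.40 for medium and large, a one-way test of three groups of 20 has power 0.37 and 0.78.

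**2. Which patients each model can use.**

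| Model | Factors | Patients used | Laser v control |
|---|---|---|---|
| Table 1 | treatment (5) x period (2) | all arms | estimable |
| Paragraph after Table 1 | wavelength (2) x site (2) | 4 x 10 = 40 of 60 | not estimable |

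The 60 is the sum of the listed arms, 4 x 10 + 20, and agrees with the Abstract.

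**3. Contrasts that match the aims.** Order the arms as 660 intraoral, 808 intraoral, 660 extraoral, 808 extraoral, control, with n = 10, 10, 10, 10, 20:

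- laser v control: (1/4, 1/4, 1/4, 1/4, -1)
- red v infrared: (1/2, -1/2, 1/2, -1/2, 0)
- intraoral v extraoral: (1/2, 1/2, -1/2, -1/2, 0)
- wavelength x site: (1/2, -1/2, -1/2, 1/2, 0)

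Every pair has sum(c1 c2 / n) = 0, so the contrasts are mutually orthogonal and together use the 4 treatment df.

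**4. Power.** Assumptions, since the article gives none: SD = 1, d = 0.8 (with 0.5 and 1.0 as a range), one time point, two-sided contrasts, no dropout. Error df = 60 - 5 = 55. For a contrast, the noncentrality is delta = |sum(c mu)| / sqrt(sum(c^2 / n)). For the omnibus test, lambda = sum n (mu - mean)^2. Critical values: F(4,55) = 2.54; t(55) = 2.00 at 0.05, 2.47 at 0.05/3, 2.58 at 0.05/4.

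- *All laser arms differ from control by 0.8.* Standard error = sqrt(1/40 + 1/20) = 0.274, delta = 2.92, lambda = 8.53.
- *Wavelength or site difference of 0.8, laser mean equal to control.* Standard error = sqrt(1/20 + 1/20) = 0.316, delta = 2.53, lambda = 6.4.

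| Pattern | d | Omnibus | Contrast, 0.05 | 0.05/3 | 0.05/4 |
|---|---|---|---|---|---|
| All laser arms v control | 0.5 | 0.25 | 0.43 | 0.27 | 0.24 |
| | 0.8 | 0.59 | 0.82 | 0.67 | 0.63 |
| | 1.0 | 0.81 | 0.95 | 0.88 | 0.85 |
| Wavelength or site | 0.5 | 0.19 | 0.34 | 0.20 | 0.17 |
| | 0.8 | 0.46 | 0.70 | 0.53 | 0.48 |
| | 1.0 | 0.67 | 0.87 | 0.75 | 0.72 |

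**5. Patterns that favour the omnibus test (d = 0.8).**

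- One site (or wavelength) works and the other equals control: omnibus 0.59; site contrast 0.70 at 0.05, 0.53 at 0.05/3, 0.48 at 0.05/4.
- Only one arm works: omnibus 0.39; laser v control 0.11 and each of the other three contrasts 0.24, all at 0.05.
- Pure wavelength-by-site interaction: omnibus 0.46; the interaction contrast 0.70, the other three only their alpha.

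**6. Multiplicity.** Treated as independent tests at 0.05 each, three contrasts give a family-wise error of 1 - 0.95^3 = 0.14 and four give 1 - 0.95^4 = 0.19.

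**The case against.** A reader might infer that a third of the patients will be discarded and laser against control never tested. The article does not say so. The only model it tabulates has five treatment levels, and treatment by period is itself a two-way layout in which the control has a cell. The wavelength-by-site sentence also goes on to count 20 controls, which suggests they are meant to be used somewhere. This stands: the loss of the controls follows from one of two readings. What remains is that the article gives both and does not choose.

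A reader might also say that the omnibus test wastes power. That holds only for the questions in the Background, and most clearly when each contrast is tested at 0.05. With alpha split, the advantage is small (0.63 or 0.67 against 0.59; 0.48 or 0.53 against 0.46) and reverses if one site equals control. If only one arm works, the omnibus test is better even against contrasts at 0.05. The Background makes that pattern plausible, since it reports pain reduction only in studies of intraoral red laser. However, a significant omnibus test still does not show which question was answered. If the follow-up were an all-pairs Tukey-Kramer test (critical t 2.82), a single arm against control would have power 0.24 at d = 0.8. The article names no such test, and a Dunnett comparison would give about 0.32.

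Leaving the post hoc test unnamed is ordinary detail for a statistical analysis plan and is no defect in itself. Nor does the text say that the test will be picked after the data are seen.

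**Conclusion.** The point holds as a failure to fix one model. The sample-size section describes two incompatible analyses, the Statistical analysis section does not say which one it means, and under one of them the first aim cannot be tested. This rests on the text alone and needs no assumption about effect size.

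The case for planned contrasts is secondary and conditional. They answer the stated questions directly. At an assumed d = 0.8 and 0.05 per contrast, they raise power from 0.59 to 0.82 for laser v control and from 0.46 to 0.70 for wavelength or site. The size of the gain depends on the alpha rule and the true effect pattern. The figures are for one time point. Analysing two occasions would change them by an amount that depends on the within-patient correlation, which the article does not state.

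**What to change.** Reconcile the two sections to one repeated-measures model with a five-level treatment factor and period, keeping all 60 patients. Remove the wavelength-by-site description as a separate model, or restate it as contrasts within the single model.

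Prespecify the four orthogonal 1-df contrasts: laser v control, red v infrared, intraoral v extraoral, and wavelength by site. State whether each applies at day 2, at day 7 or averaged over both, and how alpha is handled across the four. Report arm-level estimates with confidence intervals to serve the four-parameter comparison in the Discussion and to show a one-arm effect if there is one.

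Table 1 then needs redrawing. Its total of 49 matches 50 patients measured once. Sixty patients on two occasions give 119 df: treatment 4, between-patient residual 55, period 1, treatment by period 4, within-patient residual 55. The counts of 40, 50 and 60 patients in the text should be aligned at the same time.

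The cost is wording only. Data collection is under way, and no patient, visit or procedure changes. The price is lower power for any single contrast if only one arm works.

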## Discussion

Because virtually all patients experience pain, swelling, and muscle spasm as complications found in virtually all patients following oral surgery for the removal of bone and teeth (especially third molars) and these symptoms have a profound effect on QOL in the first few days after surgery [29-36] this model has been widely used to evaluate the effect of LLLT on the inflammatory process involving bone, connective tissue and the muscles involved in mastication [1,11-17,20-23]. In addition, removal of impacted third molars is one of the most common procedures in oral surgery [1,34,36]. However, the lack of standardization in studies with regard to the samples, methods and LLLT parameters complicates the determination of the actual effect of laser therapy on this model [1]. The aim of the present study is to use a randomized, controlled, double-blind trial to compare four different LLLT parameters in relation to the outcomes of pain, swelling and muscle spasm following surgery for the extraction of impacted third molars.

## Trial status

At the time of submission of the manuscript, the study is in the data collection phase.
